### Sample Size Determination

This study will be conducted in a total of 270 patients: a prospective control group (*N* = 108), a retrospective control group (*N* = 54), a prospective 3D printed intervention arm (*N* = 54), and a prospective 3D virtual intervention arm (*N* = 54).

The sample size (*N* = 270) was computed based on a two‐arm study at 0.05 significance level in combination with Dunnett's correction, 0.75 power size, 0.25 interesting treatment effect, and equal standard deviations of 0.5 across arms for a normally distributed primary outcome using a ‘multiarm’ web tool (https://mjgrayling.shinyapps.io/multiarm) [18]. Based on our eligibility criteria controlling for patients with pT2 and pT3 lesions, we hypothesise that we will observe a PSM rate of approximately 20% in our control group, as evidenced from previous studies [15, 19].

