### Data Analysis

For analysis, we will report contingency tables, whereby the primary outcomes will be treated as categorical variables. We will use Pearson's chi‐squared probability distribution to compare the three groups (two interventional and one control), whereby both independent (treatment: 3D virtual or 3D printed models) and dependent (PSMs) variables are categorical. Our null hypothesis is that there is no difference among these three groups. We will conduct analysis at the significance level of *P* = 0.05. We will report mean, variability and CIs for the control group and intervention arms of PSMs and functional outcomes. When analysing continuous variables resulting from questionnaires related to functional outcomes, we will conduct parametric (one‐way anova) and non‐parametric (Kruskal–Wallis test) tests depending on the tests of normality, and run an ancova, while adjusting for multiple comparisons (e.g. Bonferroni) and including pairwise comparisons (independent *t*‐tests).

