## Discussion

The identification of number and size of prostate cancer lesions prior to RARP has been limited to the 2D view of mpMRI scans and biopsy results. Surgeons are expected to mentally construct and visualise the exact location and dimensions of the lesions in 3D format prior to surgery [10]. The aim of prostate cancer surgery is to preserve maximum nerve function whilst preventing PSMs in order to achieve good functional outcomes. To accomplish this, a better understanding of prostate cancer lesions and the surrounding anatomy is needed [14]. 3D modelling has the potential to enhance surgical planning by providing surgeons with an intra‐operative navigation tool to better appreciate the nature of lesions [11].

A few studies have been conducted using either 3D virtual models or 3D printed models for RARP. Despite varying results, a number have shown a decrease in PSM rates irrespective of the model used; however, only one showed a statistically significant improvement [15]. That study, by Checcucci et al. [20], involved a total of 800 patients, with 3D virtual models created for 640 of these patients. The authors showed a PSM rate of 25% in the 3D virtual model group vs 33% in the control group [20]. To date, most studies have not used inclusion criteria that involve type of lesion, location of lesion, tumour stage or Gleason score [10, 11, 20, 21, 22, 23]. Because a lesion location that is close to the capsule or NVBs can make a significant difference to how conservatively the surgeon approaches the NVBs and the likelihood of PSMs, we have decided to exclude anterior lesions and lesions located far from the capsule to assess the true impact of the models. In addition, most studies have looked at either 3D virtual or 3D printed models [15]. In order for us to assess which is more effective in a similar cohort of patients at a single centre, we have chosen to compare both. This will help us further decide which type of model to use for a randomised controlled trial in the future.

Despite evidence showing a reduction of PSMs, comparatively few data are available showing the impact of 3D prostate models on functional outcomes, with a recent meta‐analysis showing no clear difference in postoperative and functional outcomes in the intervention groups [15]. For this reason, we will follow up patients at regular intervals for up to a year to assess the effects on incontinence and potency.

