The surgical lead for this proposal has run an Idea, Development, Exploration, Assessment, Long‐term follow‐up (IDEAL) Phase 2a study on the use of patient‐specific 3D printing in RARP in a cohort of 10 patients with intermediate and high risk of prostate cancer (T3 stages). Despite the small sample size, the outcomes of this study were crucial: PSM rates were reduced from ~35% to 10% [14]. In this study, improvement in tactile appreciation of the size, number and location of the lesions via 3D printing may have proved useful.

In all the work mentioned above, manual delineation of organs on medical images is required, a process known as medical image segmentation. Prostate segmentation is typically performed manually on preoperative T2‐weighted MRI to produce a 3D anatomical shape of the prostate gland, whereas prostate cancer lesion segmentation is conducted manually on mpMRI to generate 3D representations of the location of cancer lesions. Both tasks are time‐consuming and require substantial radiological expertise. Moreover, manual segmentation is not scalable and is prone to human error. Therefore, a reliable automated approach for prostate and cancer lesion segmentation is crucial to overcome some of the limitations of translating 3D virtual models and 3D printed models into clinical practice and into the operating theatre.

Our group has recently made substantial progress towards the automated segmentation of the prostate gland and cancer lesions, developing technologies that are timely and innovative for this proposal. In particular, our group has designed MONAI Labels, a labelling and learning tool that helps researchers and clinicians rapidly build artificial intelligence models to create segmentation datasets, for use in a study currently under review [24].

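### The 75% power statement does not fit a binary PSM endpoint with a 20% control rate or the planned three-group chi-squared test, and the stated inputs do not give N = 270

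*Protocol article*

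**What the plan says.** The Sample Size Determination section gives four groups: 108 prospective controls, 54 retrospective controls, 54 printed-model patients and 54 virtual-model patients. It says the total of 270 was computed for a two-arm study "at 0.05 significance level in combination with Dunnett's correction", with "0.75 power size, 0.25 interesting treatment effect, and equal standard deviations of 0.5 across arms for a normally distributed primary outcome". It does not state whether the test was one- or two-sided, which type of power was meant, or the allocation ratio entered. The paragraph then adds that "we hypothesise that we will observe a PSM rate of approximately 20% in our control group". No target rate for the intervention arms is given.

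The Control Group section aims for 1:2 propensity-score matching of intervention patients to controls. The Data Analysis section treats PSM as categorical and applies Pearson's chi-squared "probability distribution to compare the three groups (two interventional and one control") at the 0.05 level.

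The Discussion gives two external benchmarks. One is a cited study with "a PSM rate of 25% in the 3D virtual model group vs 33% in the control group". The other is a 10-patient pilot in which "PSM rates were reduced from ~35% to 10" per cent.

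**The concern.** Three parts of the plan do not fit together.

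- **Effect and control rate.** The effect used for sizing cannot occur at the control rate assumed in the same paragraph.
- **Sizing and analysis.** The calculation compares normal means with Dunnett's correction. The analysis is an omnibus, non-directional test on a binary outcome.
- **Total.** The 270 patients are presented as the output of the calculation.

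PSM is the primary outcome, its reduction is the main hypothesis, and the results are meant to help choose the model type for a later randomised trial. If the 75% is taken at face value, a non-significant result could be read as evidence against the models when the study had a low chance of detecting a moderate fall in PSM.

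**Working it through.** **1. Reproducing 54 per arm.** Inputs from Sample Size Determination: alpha 0.05 with Dunnett's correction, two experimental arms, effect δ = 0.25, SD σ = 0.5, power 0.75. Let k be the number of controls per patient in each intervention arm. The two test statistics have correlation ρ = 1/(1+k), and c is the Dunnett critical value.

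- *One-sided, k = 1, marginal power (one given arm significant).* c = 1.916 and n = (1 + 1/k)(σ/δ)²(c + 0.674)² = 2 × 4 × (2.590)² ≈ 53.7, so 54 per group and 3 × 54 = **162** in all.
- *One-sided, k = 2, conjunctive power (both arms significant).* c = 1.936. At 54/54/108 the standard error is 0.5 × √(1/54 + 1/108) = 0.0833, so the standardised effect is 0.25/0.0833 = 3.0. The probability that both statistics exceed c, with ρ = 1/3, is 75.4%. Solving for 75% gives 53.6 per arm and 107.2 controls, that is 54 + 54 + 108 = **216**.
- *Same 54/54/108, marginal power.* Φ(3.0 − 1.936) = 85.6%.
- *Two-sided.* k = 1 gives 67 (marginal) or 84 (conjunctive) per group. k = 2 gives 51/51/101 (marginal) or 65/65/130 (conjunctive). None gives 54.

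Both routes to 54 are one-sided, and the article does not say which was used. Neither gives 270: the total is reached only by adding the 54 retrospective controls, 216 + 54. If those were counted in the comparison (162 controls, k = 3), one-sided power would be 89% marginal or 81% conjunctive, not 75%.

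**2. Inputs against the endpoint.** For a proportion p the SD is √[p(1 − p)]. At p = 0.20 it is √0.16 = 0.40; a value of 0.5 requires p = 0.50. The sizing effect applied to the assumed control rate gives 0.20 − 0.25 = −0.05, which is not a possible rate.

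**3. Power of the planned test.** Assume 54 + 54 intervention patients, the 108 prospective controls as the single control group, and a Pearson chi-squared with 2 degrees of freedom at 0.05 (critical value 5.991). The noncentrality is λ = Σ nᵢ(pᵢ − p̄)² / [p̄(1 − p̄)]. For 20% versus 10% in both arms, p̄ = 0.15 and λ = (108 × 0.05² + 108 × 0.05²)/0.1275 = 0.54/0.1275 = 4.24. The approximate power is 43.7%; simulation gives 42%.

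| Control vs intervention PSM | Power (simulated) |
|---|---|
| 20% vs 10%, both arms | 42% |
| 20% vs 10%, one arm only | 30% |
| 20% vs 15%, both arms | 11% |
| 33% vs 25%, both arms (cited study's rates) | 19% |
| 20% vs 7%, both arms | 70% |
| 20% vs 6.5%, both arms | 75% |
| 20% vs 6%, both arms | 80% |
| 35% vs 10%, both arms (pilot's rates) | 99% |

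The choice of control group does not rescue the figure. For 20% versus 10% in both arms, power is about 33% with 54 controls and 48% with all 162. One-sided Dunnett comparisons on the binary outcome with 108 controls give about 37% per arm and 19% for both arms significant.

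**The case against.** **The 75% can be reproduced.** This is the strongest defence, and it stands. With two controls per intervention patient, in line with the 1:2 matching, a one-sided Dunnett design with conjunctive power gives exactly 54/54/108 at 75.4%. A reader who tried only marginal power might infer that 75% is an arithmetic error, that the true figure is 86%, or that the design was really derived as 162 patients. The article supports none of these. The 75% and 86% are two definitions of power for the same design, and the text does not say which route was taken.

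**A condensed article may leave sidedness, power type and allocation ratio to the full protocol.** That is fair for those omissions taken alone. It does not cover an effect and a control rate that contradict each other within one paragraph, or a total of 270 attributed to inputs that do not yield it.

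**The pilot's fall of 25 points matches the sizing effect, and an SD of 0.5 is the largest a binary outcome can have.** Both are true. The SD alone errs on the safe side, and at 35% versus 10% the planned test is well powered. So it would be wrong to say that the study cannot detect any effect its own sources suggest. But 35% is not the control rate the protocol assumes, and the pilot had 10 patients.

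**This is a non-randomised feasibility study that already plans confidence intervals.** That limits the harm. It does not remove the stated power, the significance test on PSM, or the intended use in planning a randomised trial.

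**Conclusion.** The concern holds in this form: the power statement describes a normal outcome and an effect that cannot occur at the assumed 20% control rate, and it was computed for a different test from the one planned. For the analysis as written, power is about 42% for a fall from 20% to 10% in both arms, 30% if only one arm halves, 11% for 20% versus 15%, and 19% at the cited study's rates. It reaches 75% only when both arms fall to about 6.5%. Only an effect like the pilot's, from a control rate of about 35%, is well powered.

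These figures assume independent groups, the prospective controls as the single control group, and full recruitment of 54/54/108. The intervention rates in the 20% scenarios are assumptions made here, because the protocol states none. The impossibility of a 0.25 fall from 20% depends on none of these assumptions. The claim that 270 was computed is wrong as written under either route that gives 54 per arm, since the retrospective controls belong to neither.

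**What to change.** Keep enrolment as planned and rewrite the Sample Size Determination paragraph.

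1. Replace the normal-outcome statement (effect 0.25, SD 0.5) with power for binary PSM under the planned three-group chi-squared with 54/54/108, at control rates of 20% and about 33–35%. For example: with 108 prospective controls and 54 patients per intervention arm, power at the 0.05 level is about 42% if PSM falls from 20% to 10% in both arms and 75% if both fall to about 6.5%; it is about 19% for 33% versus 25% and about 99% for 35% versus 10%.
2. State the sidedness, type of power and allocation ratio actually used in the original calculation. The authors must supply these from their own records; they cannot be inferred from the article.
3. Say that the 54 retrospective controls are additional to that calculation.

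The cost is one paragraph and no extra patients. The downside is that the stated power becomes less favourable.

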### Methods of Data Collection

This will be a single‐centre study performed in the Urology Department of Guy's Hospital, London, UK. Specimen analysis will be carried out on the whole prostate gland removed from the patient during RARP to evaluate margin status and estimate PSMs. There will be no deviation from normal clinical practice.

At the 6‐week follow‐up, the surgeon will meet with the patient to present PSM status and capture functional outcomes from the patient via questionnaires. We will capture these measures as endpoints for analysis. These questionnaires will be re‐administered at 3, 6 and 12 months postoperatively.

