**Patients and Methods:**

The study will consist of a total of 270 patients: 54 patients will be included in each of the interventional groups (3D virtual, 3D printed models), 54 in the retrospective control group and 108 in the prospective control group. Automated segmentation of prostate gland and lesions will be conducted on multiparametric magnetic resonance imaging (mpMRI) using ‘AutoProstate’ and ‘AutoLesion’ deep learning approaches, while manual annotation of the neurovascular bundles, urethra and external sphincter will be conducted on mpMRI by a radiologist. This will result in masks that will be post‐processed to generate 3D printed/virtual models. Patients will be allocated to either interventional arm and the surgeon will be given either a 3D printed or a 3D virtual model at the start of the RARP procedure. At the 6‐week follow‐up, the surgeon will meet with the patient to present PSM status and capture functional outcomes from the patient via questionnaires. We will capture these measures as endpoints for analysis. These questionnaires will be re‐administered at 3, 6 and 12 months postoperatively.

Abbreviations2Dtwo‐dimensional3Dthree‐dimensionalmpMRImultiparametric MRINVBneurovascular bundlePSMpositive surgical marginRARProbot‐assisted radical prostatectomy

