### Study Design

This is the design for a single‐centre parallel feasibility study consisting of two prospective intervention arms (a 3D printed model and a 3D virtual model), and a retrospective and a prospective control group (Fig. 1). Although this study will be non‐blinded for surgeons as they will be operating on patients using either of the models, it will be blinded for analysis. Note that this will not be a randomised study.

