### Endpoints

The primary study outcome is PSM rates measured after specimen analysis. Secondary outcomes include incontinence rates (pad weights, electronic Patient‐Reported Outcome Measures), erectile dysfunction (International Index of Erectile Function score, and Erectile Hardness Score), and International Consultation on Incontinence Questionnaire‐Urinary Incontinence (ICIQ‐UI) score captured at 3 months after surgery. Other secondary outcomes are related to our pipeline deployment metrics, including patient recruitment rate and percentage of cases that led to successful model deployment in the theatre.

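### At 6 weeks an unblinded surgeon both gives the margin result and collects the patient-reported functional endpoints; patients should complete the questionnaires themselves, away from the surgeon

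*Protocol article*

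**What the plan says.** Methods of Data Collection describes one 6-week visit at which "the surgeon will meet with the patient to present PSM status and capture functional outcomes from the patient via questionnaires". The Abstract has the same sentence, and both places add "We will capture these measures as endpoints for analysis". Later collection is covered by "These questionnaires will be re‐administered at 3, 6 and 12 months postoperatively", with no statement of who collects.

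On blinding, the Study Design section says "this study will be non‐blinded for surgeons as they will be operating on patients using either of the models" and, for the rest, "it will be blinded for analysis". It also says "Note that this will not be a randomised study".

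The Endpoints section lists the functional outcomes: pad weights, electronic patient-reported measures, two erectile function scores and the ICIQ-UI. The list ends "score captured at 3 months after surgery", a time point that applies at least to the ICIQ-UI. Under Interventions, the baseline questionnaires are filled out by patients in the clinic and stored on REDCap.

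**The concern.** Apart from pad weights, the functional outcomes are the patient's own account of continence and erections. The person named as capturing them at 6 weeks knows the arm, and at the same visit tells the patient his margin status, which is the study's primary outcome.

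Two distinct biases are possible:

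- **Disclosure.** A man just told of a positive margin may answer differently from one told that his margins are clear. If positive-margin rates differ between arms, the average effect on answers differs too.
- **Reporting to an unblinded collector.** A patient may soften his answers to his surgeon, and a surgeon who knows the arm may prompt or frame questions differently.

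The study's main hypothesis includes better function with a model, so an arm-specific shift in that direction would look like a benefit. Without randomisation, such a shift would add to confounding and could not be separated from it. Neither blinding the analyst nor adjusting for baseline corrects answers that were shifted when they were given.

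**Working it through.** No figure in the Protocol article bears on this point, so there is nothing to reproduce. The sizes below illustrate the risk; every bias input is an assumption.

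**Inputs from the document.** 54 patients per intervention arm and 108 prospective controls (Sample Size Determination); control positive-margin rate about 20% (same section); significance level 0.05, with adjustment for multiple comparisons of which Bonferroni is given as an example (Data Analysis).

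**Step 1: precision.** For one intervention arm against the prospective controls, the standard error of a standardised mean difference is

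SE = √(1/54 + 1/108) = √0.02778 = 0.1667 SD.

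**Step 2: disclosure.** Between-arm bias = (control rate − arm rate) × (shift in score, in SD, caused by being told of a positive margin). Arm rates of 5% to 15% and shifts of 0.2 to 0.8 SD are assumed.

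| Arm rate (control 20%) | shift 0.2 SD | shift 0.5 SD | shift 0.8 SD |
|---|---|---|---|
| 15% | 0.01 | 0.025 | 0.04 |
| 10% | 0.02 | 0.05 | 0.08 |
| 5% | 0.03 | 0.075 | 0.12 |

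The range is 0.01 to 0.12 SD. If there is no difference in margin rates and no difference in how the news is framed, this bias is zero.

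**Step 3: false-positive rate for a bias b with no true effect.** For a two-sided test with critical value c,

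P(reject) = Φ(b/SE − c) + Φ(−b/SE − c).

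With c = 1.96, disclosure biases of 0.02, 0.05, 0.08 and 0.12 SD give 5.2%, 6.0%, 7.7% and 11.1%.

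For reporting to an unblinded collector, between-arm shifts of 0.1 to 0.3 SD are assumed. The last column takes Bonferroni over the three pairwise comparisons of three groups, 0.05/3, c = 2.394.

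| b (SD) | b/SE | one test at 0.05 | one test at 0.05/3 |
|---|---|---|---|
| 0 | 0 | 5% | 1.7% |
| 0.1 | 0.6 | 9% | 4% |
| 0.2 | 1.2 | 22% | 12% |
| 0.3 | 1.8 | 44% | 28% |

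For example, b = 0.2 at 0.05: Φ(1.2 − 1.96) + Φ(−1.2 − 1.96) = 0.224.

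**Step 4: what each remedy reaches.**

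| Change | Disclosure, 6 weeks | Disclosure, 3 to 12 months | Unblinded collector |
|---|---|---|---|
| Questionnaire before result, surgeon still collects | removed | not removed | not removed |
| Self-completion without the surgeon, before the 6-week consultation, same route later | removed | not removed | removed as a route |

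Changing the order alone therefore deals only with the smaller component, and only at 6 weeks.

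**The case against.** The strongest reply is that the text says less than it seems to. It names two purposes of one visit and fixes no sequence. It says only that it is the surgeon, not the one who operated. Capture through questionnaires need not mean an interview: baseline forms are filled out by patients and electronic measures are planned, so self-completion at 6 weeks may be intended. Who is in the room is a detail that an article can leave to the full protocol.

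Much of this stands. The order is implied, not fixed, and that the collector performed the operation is a reasonable inference rather than a statement. What remains is that the article names an unblinded surgeon as the person capturing these endpoints, in both places where it describes the visit.

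A second reply is that a wish to please the surgeon would largely cancel if every arm is followed up in the same way, and the article describes one visit without distinguishing arms. That is right: only the part that differs by arm biases the comparison, and the documents do not show how large that part is. The unadjusted error rates also overstate the position under the planned multiplicity adjustment, as the table shows.

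Third, the Endpoints section sets at least the ICIQ-UI at 3 months, so the 6-week visit is not the only functional time point, and perhaps not the main one. This also stands, and it is why the remedy has to cover the later visits.

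A reader might infer that asking the questions before giving the result would cure the problem. The documents do not support that: the same unblinded surgeon would still collect the answers, and by 3 months the result is known whatever the order at 6 weeks.

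**Conclusion.** The point holds as a weakness in how the functional endpoints are collected, not as an error or contradiction. A surgeon who is not blinded to arm captures patient-reported endpoints at the visit where the margin result is given, and blinded analysis does not protect against bias introduced there.

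The disclosure component is probably small: 0.01 to 0.12 SD, assuming arm margin rates of 5% to 15% against 20% and a 0.2 to 0.8 SD reaction to the news. The collector component could be larger, but its size is unknown. The 9% to 44% range assumes a true between-arm shift of 0.1 to 0.3 SD, full recruitment of 54 and 108, and one unadjusted test; at 0.05/3 it is about 4% to 28%. These rates show how sensitive the comparison is. They do not estimate a bias known to be present.

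A reader might also infer that the main result is compromised. It is not: margin status comes from specimen analysis, and pad weights do not depend on this route. The change is worth making because it is cheap and cannot be made once the answers have been collected.

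**What to change.** Amend Methods of Data Collection, and the matching sentence in the Abstract, to say that:

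- patients complete the functional questionnaires themselves, on the electronic measures already listed under Endpoints, without the surgeon present;
- at 6 weeks this is done before the consultation and before the margin result is given, with completion time-stamped;
- the same self-completed route is used at 3, 6 and 12 months and in all prospective groups, including the prospective controls.

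The surgeon still gives the margin result at the same 6-week visit, so the consultation itself is unchanged. The retrospective controls lie outside this change.

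The cost is minor: a few minutes or a link before the visit, and reminders for some patients. The electronic measures and REDCap are already in the plan. Self-completion does not remove the effect of knowing the margin result at the later visits, and the report should say so.
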